## Methods

### Pre-testing standardisation procedures

Participants will attend the Deakin University, Burwood laboratory for two visits: pre-intervention (baseline) and post-intervention (12-weeks). All visits will be conducted following an overnight fast of at least 12 h.

To ensure adequate carbohydrate availability prior to the oral glucose tolerance test (OGTT) and to prevent a false-positive results [42], participants will be provided with a standardised pre-packaged evening meal to be consumed the night before each laboratory visit. Participants will be offered either a meat-based or vegetarian pre-packaged pasta dish, both matched for energy (1780–1900 kJ) and macronutrient composition, particularly carbohydrate content (~ 50–55 g), in accordance with best practice recommendations for OGTT preparation [42]. Participants will also be asked to refrain from drinking alcohol or exercising 24 h prior to each laboratory visit.

On the morning of testing, participants will be asked to consume 500 ml of plain water 45–60 min prior to their arrival. This hydration protocol is based on best practice guidelines to standardise hydration status for dual energy X-ray absorptiometry (DXA) scanning (DPX-IQ Lunar; Lunar Corporation, Madison, WI) [43]. In our previous studies, we have demonstrated that this approach results in consistent hydration status across testing sessions, with a coefficient of variation (CV) of 0.9% between pre- and post-intervention measures for lean muscle mass, measured using DXA, indicating excellent reproducibility [44].

Hydration status will be assessed using urine specific gravity (USG), measured via digital refractometry (PAL-10 S; Atago Co., Ltd., Tokyo, Japan). Following hydration assessment, the testing day will proceed in the following order: anthropometric measurements, DXA scan, fasting blood collection and OGTT, post-test standardised meal, followed by assessments of muscle strength and cardiorespiratory fitness. All efforts will be made to ensure the participants follow this order for both pre- and post-testing.

### Anthropometric assessment

At the commencement of the pre-testing visit, standardised anthropometric measurements including height (to the nearest 0.1 cm using a wall-mounted stadiometer) and body mass (to the nearest 0.1 kg using a calibrated digital scale (model UC-321; A&D Medical, Tokyo, Japan) will be recorded.

### Primary outcomes: body composition

The primary outcomes will be the mean percentage change (± standard deviation, SD) in total body and regional lean (arms and legs) and fat-free mass (FFM), assessed using DXA (Lunar Corp., Madison, WI). All DXA scans will be conducted by trained personnel experienced in the use of DXA technology and certified in accordance with standard operating procedures for body composition analysis. In addition to lean mass, total (kg) and relative (%) fat mass and visceral fat mass will also be reported as will the delta changes from pre-post training.

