**Methods:**

This protocol outlines a 12-week study comprising a 10-week supervised resistance and HIIT intervention, with baseline and post-intervention assessments conducted over one-week periods immediately before and after the intervention. The randomised, double-blind, placebo-controlled trial will investigate the effects of defatted APP supplementation in postmenopausal women. We aim to recruit 48 participants who will be randomly allocated to receive either APP or an energy-matched placebo (maltodextrin). Primary outcomes include changes in total and regional lean mass which will be assessed using dual-energy X-ray absorptiometry (DXA). Secondary outcomes include strength, assessed via 3-repetition maximum (3-RM) chest press and leg press, and maximal handgrip strength; cardiovascular fitness (VO₂peak); total body fat (absolute and %), blood lipids; blood glucose; insulin response; appetite; supplement acceptability; and dietary intake. Data will be analysed using linear regression and mixed-effects models under intention-to-treat and per-protocol frameworks.

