## Objectives

The primary objective of this study is to evaluate the additive effects of defatted APP, beyond those induced by exercise training alone, on lean muscle mass in postmenopausal women undertaking a 10-week, fully supervised resistance and high-intensity interval training (HIIT) program.

Secondary outcome measures include between-group differences in muscular strength and aerobic fitness; body composition (including total and regional fat mass); cardiometabolic health markers, including blood glucose and insulin sensitivity, derived from an oral glucose tolerance test (OGTT) and calculated using validated surrogate indices (e.g. the Matsuda insulin sensitivity index and/or HOMA-IR derived from fasting values); lipid profiles; appetite regulation and taste preference; and dietary intake patterns, with a specific focus on protein and fibre intake.

Given that both groups complete an identical exercise intervention, all secondary outcomes will be interpreted as reflecting the incremental contribution of APP supplementation, relative to an energy-matched placebo, rather than the independent effects of exercise or fibre alone. Outcomes will be assessed at baseline and following the 10-week intervention.

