#### Data analysis

Participant withdrawals and missing data will be documented, with primary analyses conducted under an intention-to-treat (ITT) framework and secondary per-protocol analyses based on predefined adherence criteria. A secondary, per-protocol analysis will be carried out to include only participants that attend ≥ 80% of their training sessions and consumed ≥ 80% of their supplement over the course of the study. Between-group comparisons will be conducted using linear models, adjusting for baseline values. Outcome variables will be log-transformed where necessary to meet the assumptions of parametric testing. Within-group changes will be evaluated using appropriate statistical tests, such as mixed-models. All statistical analyses will be two-tailed, with significance set at *p* < .05. Multiple imputation by chained equations will be used to handle missing data.

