#### Sample size and statistical power

As no established minimal clinically important difference exists for fat-free mass (FFM) or lean mass, as an alternative, sample size was justified on several factors: (1) based on biological aging trajectories; older adults typically experience a decline of approximately 0.5–1.0 kg per year in FFM [64, 65], equating to an estimated 1–2% annual loss. A 2.0% increase in lean mass in the intervention group may therefore be interpreted as a reversal of two years’ worth of age-related muscle loss; (2) in similar studies in this age group, the non-supplemented group may see a non-significant improvement of their lean mass of ~ 0.2–0.4% following 12-24-weeks of resistance training [66], whilst the intervention group supplemented with protein may improve lean mass by a magnitude of 2.4% [67]. Similarly, our own data with strength training 2x week in women supplemented with protein demonstrated an increase in lean mass of 2.7% [44]. The study was therefore powered to detect a between-group difference of 2.0% in FFM change (control: 0.4%; supplemented: 2.4%). Assuming a standard deviation of 2.2% (calculated from raw data from [name], Silver [44], this requires a sample size of 42 participants (21 per group) to achieve 80% power at a at α = 0.05 and accounting for an anticipated 10% dropout rate we will aim to recruit 48 participants in total.

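### Four body-composition measures are primary and each is tested at p < .05, but only fat-free mass is powered, so the chance of a false primary success is well above 5%

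*Protocol article*

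**What the plan says.** The primary quantity is described in four places, each time differently.

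- **Primary outcomes: body composition:** several outcomes, in the plural, each a percentage change in "total body and regional lean (arms and legs) and fat-free mass (FFM"), measured by DXA. The plain reading is four variables: total lean mass, arm lean mass, leg lean mass and FFM.
- **Abstract, Methods:** "Primary outcomes include changes in total and regional lean mass". The plural is kept, but FFM is not named.
- **Objectives:** the effect of the supplement "on lean muscle mass in postmenopausal women undertaking a 10-week, fully supervised resistance and high-intensity interval training (HIIT) program". This is one construct, and no variable is chosen.
- **Sample size and statistical power:** the trial is "powered to detect a between-group difference of 2.0% in FFM change". This is one variable. The supporting argument moves between FFM and lean mass.

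On testing, the Data analysis section says: "All statistical analyses will be two-tailed, with significance set at *p* < .05". The protocol states no order of testing, no division of alpha, and no rule on whether one primary outcome or all of them must be significant.

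**The concern.** With several primary outcomes, each tested at the full 5% level, and no rule for success, a significant result on any one of them can be reported as a positive primary finding. The 5% error rate then holds for each test but not for the trial's headline claim.

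Two further problems follow. Arm and leg lean mass are primary but have no stated power. And because the sections disagree on which variable is primary, the choice of which to headline stays open until results are available.

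**Working it through.** **1. The plan's own sample size.** Inputs from Sample size and statistical power: difference 2.0 percentage points (0.4% against 2.4%), SD 2.2%, two-sided α = 0.05, power 80%, equal groups, 10% dropout.

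- Standardised difference: 2.0 / 2.2 = 0.909.
- The normal approximation gives 19 per arm. The exact two-sample t-test (noncentral t) gives 20.002, rounded up to 21 per arm, or 42 in total. Power at 21 per arm is 0.820.
- Dropout: 42 / (1 − 0.10) = 46.7, so 47, or 48 as an even number.

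The stated 42 and 48 are reproduced. They cover one outcome at the full 5% level.

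**2. False-positive rate if any one primary outcome suffices, with independent tests.** The formula is 1 − (1 − 0.05)^k.

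| Reading | k | Rate |
|---|---|---|
| Abstract (total, arms, legs) | 3 | 1 − 0.95³ = 14.3% |
| Primary outcomes section | 4 | 1 − 0.95⁴ = 18.5% |
| Same section, with regional also applied to FFM | 6 | 1 − 0.95⁶ = 26.5% |

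These are upper figures, because the measures overlap.

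**3. Allowing for correlation.** The protocol gives no correlations, so those below are assumptions. Two-sample t-tests with 21 per arm were simulated with no true effect on any outcome, 100,000 runs per scenario. The t-test stands in for the planned linear model adjusted for baseline.

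| Common correlation | Four outcomes | Three outcomes |
|---|---|---|
| 0.5 | 15.8% | 12.7% |
| 0.7 | 13.3% | 11.0% |
| 0.8 | 11.5% | 9.8% |
| 0.9 | 9.4% | 8.3% |
| 0.95 | 8.1% | 7.4% |

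A more realistic structure treats total lean mass and FFM as nearly the same measure (r = 0.99) and lets the limbs vary:

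| Total–arms | Total–legs | Arms–legs | Rate, four outcomes |
|---|---|---|---|
| 0.40 | 0.50 | 0.20 | 13.8% |
| 0.50 | 0.70 | 0.30 | 13.0% |
| 0.70 | 0.80 | 0.50 | 11.6% |
| 0.85 | 0.90 | 0.75 | 9.6% |

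**4. Keeping four primaries and controlling the error.** Bonferroni gives α = 0.05 / 4 = 0.0125 per test. For the same FFM effect, power at 21 per arm falls from 0.820 to 0.630. Restoring 80% power needs 28.6, so 29 per arm: 58 evaluable, and 58 / 0.90 = 64.4, so 65 recruited, or 66 as an even number.

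**5. Power for the regional measures.** The protocol gives no SD for arm or leg lean mass. If the SD of percentage change were 3% or 4% (assumption) and the difference again 2 points, power at 21 per arm and α = 0.05 would be 56% or 35%.

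**The case against.** The strongest reply has four parts.

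- **The count and the label.** The key sentence is loose, and the abstract implies three outcomes. Total lean mass and FFM are used almost as synonyms, and the effects cited in the sample size section are lean-mass figures, so power for one is close to power for the other. This is fair. It means that 18.5% should not be quoted as the actual error rate, and that arm and leg lean mass are the measures truly without power support. It does not bring the rate near 5%: three outcomes at r = 0.9 still give 8.3%.
- **No rule that any one outcome wins.** The protocol never says that one significant outcome is enough, and an analysis plan could add a multiplicity procedure. Silence on the procedure alone would not be a finding. But this protocol positively fixes several primaries and 5% for every analysis, and it names the primary differently in four places. A later plan that divided alpha would contradict the Data analysis section and undercut a power calculation that uses the full 5%.
- **Blinded analysts.** Under Allocation concealment and blinding, analysts stay blinded until the primary analysis is final. This restrains choosing an outcome by direction of effect. It does not hide which outcomes differ between groups A and B, and it does nothing about multiplicity.
- **Choice of fix.** Total lean mass fits the objective and the abstract at least as well as FFM, and a fixed testing sequence would also control the error. Both are workable. They change which single or first outcome is named, not the need to name it.

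**Conclusion.** The concern holds. The protocol fixes several primary outcomes at 5% each, states no rule for success, and is inconsistent about which variable is primary. If one significant result is enough, the chance of a false primary success under no effect is about 10% to 14% in the structured scenarios, roughly two to three times the nominal level. It is 8.1% with four outcomes at a common correlation of 0.95, and at most 18.5% under independence. Every scenario exceeds 5%.

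These figures rest on assumed correlations and on the any-one-suffices reading, which nothing in the protocol excludes. The regional power figures rest on an assumed SD, and the conclusion does not depend on them. The stated sample size is correct for one outcome. Because the defect touches the trial's main claim, it must be fixed.

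**What to change.** Name one primary outcome, in the same words, in the abstract, the objectives and the section on primary outcomes: the between-group difference in percentage change in total-body FFM, the quantity already powered. Move total, arm and leg lean mass to secondary outcomes, reported with confidence intervals as supportive evidence. Make the change, with a date, before unblinding. Data collection is expected to run to October 2026 and blinding lasts until the primary analysis is final, so a change made now is still credible.

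If the sponsor prefers total lean mass, the sample size section must be rewritten to that variable. If the regional measures are to stay confirmatory, a fixed order of testing after the named primary would control the error, but their power would still need to be stated.

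The cost is wording in the protocol and the registry entry. The 42 evaluable and 48 recruited stand. The downside is that regional lean-mass results lose confirmatory status.

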### Secondary outcomes

#### Blood collection and analysis

Following the DXA scan, participants will remain in a fasted state after which a cannula will be inserted in an antecubital vein for serial blood sampling. Cannulation and blood collection will be performed by a certified member of the research team (e.g., medical doctor or qualified personnel such as [name], [name], and [name], all of whom are certified in venepuncture and cannulation procedures). A standard OGTT will then be administered, involving the ingestion of a 75 g/300 ml glucose solution (GTT Drink; Point of Care Diagnostics, Australia). Blood samples will be collected at 15-minute intervals from − 15 min to + 120 min post-ingestion to assess serum glucose and insulin concentrations over time.

In addition, a separate set of baseline fasting blood samples will be collected at -15 min for the analysis of blood lipid profiles, including insulin, high-density lipoprotein cholesterol (HDL-C), low-density lipoprotein cholesterol (LDL-C), triglycerides (TG), and total cholesterol (TC). Blood glucose will be analysed in-house using a HemoCue^®^ Glucose 201+ (Ängelholm, Sweden) in duplicate and the mean value will be reported. Serum insulin and other metabolic markers will be analysed by a certified commercial pathology laboratory (Dorevitch Pathology Labs, Australia) using standard clinical assays. Differences in biochemical markers from baseline will be compared between groups to evaluate changes resulting from the intervention. Upon completion of the OGTT, participants will be provided with the same standardised meal they received for pre-testing.

### Muscle strength assessment

#### Hand grip strength

Hand grip strength will be assessed with a digital handheld dynamometer (Jamar^®^ Plus+ Digital Hand Dynamometer, Sammons Preston, Bolingbrook, IL), to assess changes throughout the intervention and to assess sarcopenia risk [9]. Measurements will be taken with the participant standing, elbow positioned at their side and flexed at 90°, with the wrist in a neutral position. Participants will be instructed to squeeze the dynamometer with maximum effort using their dominant hand. This procedure will be repeated three times, with a one-minute rest between attempts. The highest recorded value from the dominant hand will be used for analysis [45].

#### 3-repetition maximum (3-RM) testing

Participants will perform a three-repetition maximum (3-RM) test to assess changes in both upper and lower body strength over the course of the intervention. Upper body strength will be evaluated using a fixed, pin-loaded chest press machine (Impulse^®^ IT9501 Chest Press, Impulse Fitness, Qingdao, China), while lower body strength will be assessed using a plate-loaded leg press machine (Body Iron^®^ Leg Press Machine, Body Iron, Melbourne, Australia). Prior to testing, participants will undergo a brief familiarisation with each resistance machine to ensure correct technique and safety. A standardised warm-up protocol will be completed, consisting of 8, 5, and 3 repetitions at 50%, 75%, and 95% of predicted 3-RM, respectively, to prepare for the 3-RM attempts [46, 47]. Participants will perform 3-RM attempts with a 2.50 kg (1.25 kg each side) minimum load increase each testing set, until 3-RM is reached. Participants will rest for 3–5 min between sets [48] and will be allowed to have 2 re-attempts at a failed lift. The outcome will be the maximal load (in kilograms) successfully lifted for three consecutive repetitions, recorded separately for chest press and leg press exercises [49, 50].

### Submaximal Incremental Bike Test (VO_2_peak)

To track changes in cardiorespiratory fitness participants will undergo a sub-maximal graded exercise test on a cycle ergometer (Lode Excaliber Sport, Lode Ergometry, Groningen, Netherlands). The test will begin at 10 watts (W), with increments of 10 watts (W) every minute until participants achieve a rate of perceived exertion (RPE) of 15 on the Borg scale, or are unable to maintain a cadence of ≥ 60 revolutions per minute (RPM) for more than 30 s. The test will also be terminated if participants request to stop or if any clinical contraindications to continued exercise arise. The highest workload completed at RPE 15 will be recorded as peak power output and used to estimate VO_2peak_. This submaximal RPE-based cycling protocol has demonstrated acceptable validity and safety in older adult populations [51–53].

### Blood pressure monitoring and safety procedures

Resting blood pressure (BP) will be assessed once participants are seated and have rested quietly for at least 5 min, prior to commencing the OGTT and exercise testing. BP will be measured using an automatic blood pressure monitor (Welch Allyn ProBP 3400 Series, NY, USA), in accordance with standard clinical guidelines [54]. If resting systolic BP is ≥ 160 mmHg, BP will be re-measured on two additional occasions (total of three measurements), with at least 1–2 min between measurements. If systolic BP remains consistently ≥ 160 mmHg across all readings, testing will be terminated and the participant will be advised to follow up with their general practitioner (GP) and obtain medical clearance prior to proceeding with the 10-week exercise intervention. If systolic BP falls below 160 mmHg in subsequent measurements, testing may proceed with caution.

Blood pressure will also be measured immediately before and immediately after the submaximal bike test (OMRON HEM-7120, OMRON Healthcare Co., Ltd, Kyoto, Japan). If systolic BP is ≥ 160 mmHg at rest prior to exercise, and remains elevated following two confirmatory measurements, the testing session will be terminated and the participant referred to their GP for further investigation.

Participants will also be monitored for hypotension, defined as BP ≤ 90/60 mmHg [54–56]. In such cases, testing will proceed with caution, and participants will be closely monitored for symptoms including dizziness, light-headedness, faintness, or loss of balance. If any of these symptoms are present, OGTT and exercise testing will not proceed, and participants will be advised to seek medical follow-up.

### Submaximal exercise protocol

#### Dietary intake monitoring

Participants will be asked to fill out a 3-day food diary using the app Easy Diet Diary (Xyris Pty Ltd, 2024) on their own personal phones for 2- weekdays and 1 weekend day. They will be asked to complete the food diary at baseline, week 2, 5, 8 and 12 (see Fig. 1). A two-page instructional guide will be provided, and a member of the research team will explain how to accurately record dietary intake using the app [57]. Dietary intake data will be analysed using *FoodWorks.online* software (Version 2.0 Professional; *Xyris Pty Ltd*, 2026). The total average daily energy, macronutrients (carbohydrates, protein and fats) and fibre intakes will be analysed. Group comparisons and within-participant changes will be evaluated to identify any significant dietary modifications over the intervention period.

### Appetite, hunger, and supplement acceptability

#### Appetite and hunger ratings

Participants will complete validated appetite questionnaires administered via REDcap. Appetite and hunger assessments will be conducted at multiple time points (see Fig. 1): in a fasted state, immediately post-training, post-recovery drink, and two hours post-recovery drink. This is to evaluate acute satiety effects of the supplement post-exercise. Appetite and hunger will be measured using a 100-mm visual analogue scale (VAS) with opposing anchors (“not at all” at 0 and “extremely” at 100). The questionnaire comprises nine items assessing subjective appetite sensations. Example items include: “How strong is your feeling of hunger?” and “How strong is your urge to eat?” (see Appendix 2 for full item list).

#### Supplement acceptability

Acceptability of the protein and placebo supplements will be assessed via a structured questionnaire administered through REDcap, completed at the same time points as the appetite visual analogue scale (VAS) assessments (i.e., fasted, post-training, post-recovery drink, and two hours post-recovery drink; see Fig. 1). The questionnaire includes a series of 7-point Likert scale items evaluating various dimensions of acceptability, including taste, ease of preparation, perceived effort, and overall satisfaction. For example, participants will rate statements such as “How much do you like the taste of the supplement?” and “How easy is it for you to prepare the supplement?” with anchors ranging from 1 (“not at all” or “extremely difficult”) to 7 (“extremely” or “extremely easy”), depending on the question context. In addition, participants will complete a 10-point scale to assess their likelihood of continued use of the supplement. Anchors range from 1 (“I would take this supplement every opportunity I had”) to 10 (“I have never tried this supplement”), enabling evaluation of habitual acceptability and intention to use. The full Supplement Acceptability questionnaire is provided in Appendix 3.

